This study seeks to 1) describe changes in adult height across cohorts 2) assess whether changes in mean height are related to changes in the dispersion of height across birth cohorts within and across countries, 3) determine whether patterns exist with regard to which parts of the height distribution experience the greatest height gains or losses across birth cohorts.

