**Analysis**

We will use a pooled dataset that includes all countries and survey waves. We will also create a second database also that includes summary percentile values and 33-quantile values for the height distribution in each country for each birth cohort. Stata v14.0 (StataCorp 2015) will be used to conduct the statistical analysis and graphics will be produced using the statistical package R (R Core Team 2013).

Research Question 1 will be addressed as follows. Summary tables that describe basic statistics of the population will be constructed according to country and birth cohort. These tables will include change in mean height and standard deviation of height for each country. An F-test for equality of variance will be performed to test the difference in SD between the earliest and most recent birth cohorts for each country.

Research Questions 2 and 3 will be addressed using both graphical and statistical approaches.

Graphical Analyses

Graphical approaches will be used to examine height within countries across birth cohorts. The first type of plot created will be the Quantile-Quantile (QQ) plot, which has previously been used to examine distributional changes in BMI (Razak, Corsi et al. 2013). QQ plots are particularly effective at depicting change at the tails of the distribution (Wilk and Gnanadesikan 1968). To construct the QQ plot, 33-quantiles (1^st^, 4^th^…94^th^, 97^th^) of height (y-axis) from the most recent birth cohort were plotted against the corresponding 33-quantiles of height (x-axis) from the earliest birth cohort for each individual country. 33- quantiles were used instead of percentiles in order to improve the smoothness of the graphical distributions. If the distribution of height remains the same across birth cohorts, regardless of overall gains or decreases in height within the country, the QQ plot will fall on the line of equality (line y=x). If segments of the QQ plot fall above the line, it indicates that certain segments of the population experienced disproportionate gains in height, while if the plot falls below the line of equality, it indicates that segments of the population experienced declines in height across birth cohorts.

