The second plot type that will be used is the mean-difference plot. Mean difference plots graph the differences between corresponding quantiles on the y-axis against the means of the same quantile on the x-axis. The point’s location on the y-axis shows the direction and magnitude of the shift in relation to its difference from the horizontal line representing zero (Flegal and Troiano 2000). Mean-difference plot will be created for each country showing the shift in distribution of height between the most recent birth cohort and the earliest birth cohort available for each country. Points that fall below the line at zero indicate losses in height at that place in the distribution, while points that fall above the line indicate gains in height.

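### The reading rule for the QQ and mean-difference plots makes no allowance for sampling error, so noise at the extreme quantiles can be read as change in the tails

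*SAP*

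**What the plan says.** The graphical part of the SAP's Analysis section specifies two plots per country, each comparing the earliest with the most recent birth cohort at 33 quantiles (1st, 4th, and so on to the 97th).

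- Mean-difference plot: "Points that fall below the line at zero indicate losses in height at that place in the distribution". The opposite side of zero is read as a gain.
- QQ plot: "if the plot falls below the line of equality, it indicates that segments of the population experienced declines in height across birth cohorts". A segment above the line is read as a disproportionate gain.

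The plan recommends the QQ plot for the extremes: "QQ plots are particularly effective at depicting change at the tails of the distribution". It gives the plots a formal role: "Research Questions 2 and 3 will be addressed using both graphical and statistical approaches". Research question 3 is to "determine whether patterns exist with regard to which parts of the height distribution experience the greatest height gains or losses across birth cohorts".

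No section attaches a confidence interval, band, minimum difference or test to a quantile difference.

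**The concern.** Both sentences move from the side of the line on which a sample quantile falls to a statement about height in that part of the distribution; the QQ sentence says outright that segments of the population underwent the decline. Two samples from the same population almost never give identical quantiles, so the rule produces gains and losses even when nothing has changed.

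The error is also uneven. Quantiles far from the centre are estimated least precisely, so under a uniform shift the tails will look more changeable than the middle. That is the pattern research question 3 looks for. At stake are per-country statements that the shortest or tallest women gained or lost height, or that the spread of height changed.

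**Working it through.** **Nothing to reproduce.** The plan gives no precision for quantile differences and no number of women per country and cohort. It gives 5000 to 30 000 households per survey and a multistage cluster design (Data Sources). What follows is an illustration.

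**Do the other analyses fill the gap?** The F-test compares SDs between the two cohorts. The multilevel models relate the SD to the mean, and the 5th and 95th percentiles to the median, pooled over all countries and cohorts. Neither asks whether a particular quantile moved in a particular country.

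**Assumptions not in the plan.** Normal heights, SD 6.5 cm, simple random sampling, two cohorts of equal size n, n from 500 to 5000.

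**Formulas.** SE of the difference at quantile p = SD × k(p) × √(2/n), with k(p) = √(p(1−p)) / φ(z_p). Chance that a true uniform gain d shows as a loss = Φ(−d / SE).

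**Relative noise, for any n.**
- Median: k = 0.5 / 0.3989 = 1.253
- 5th percentile (P5): k = 0.2179 / 0.1031 = 2.113, ratio to median 1.69
- 97th percentile (P97): k = 0.1706 / 0.0680 = 2.507, ratio 2.00
- 1st percentile (P1): k = 0.0995 / 0.02665 = 3.733, ratio 2.98

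P1 and P97 are the outermost plotted points. P5 is not plotted (the nearest point is the 4th percentile, ratio 1.81), but it is the lower tail measure that the plan models.

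**Worked case.** At P1 with n = 1000, SE = 6.5 × 3.733 × √(2/1000) = 1.085 cm. For d = 0.5 cm, Φ(−0.5/1.085) = Φ(−0.461) = 32%.

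| n per cohort | SE (cm): P1 / P5 / median | False loss, true gain 0.5 cm: P1 / P5 / median | False loss, true gain 1 cm: P1 / P5 / median |
|---|---|---|---|
| 500 | 1.535 / 0.869 / 0.515 | 37% / 28% / 17% | 26% / 12% / 2.6% |
| 1000 | 1.085 / 0.614 / 0.364 | 32% / 21% / 8.5% | 18% / 5% / 0.3% |
| 2000 | 0.767 / 0.434 / 0.258 | 26% / 12% / 2.6% | 10% / 1% / <0.1% |
| 5000 | 0.485 / 0.275 / 0.163 | 15% / 3% / 0.1% | 2% / <0.1% / <0.1% |

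A design effect of 2 is equivalent to halving n, so the row for 1000 would become the row for 500.

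**Simulation check** (1000 runs per setting, heights rounded to 0.1 cm, no clustering). With a true gain of 0.5 cm, P1 showed a loss in 35%, 31%, 26% and 12% of runs for n = 500, 1000, 2000 and 5000, close to the formula. With identical cohorts, at least one of the 33 points fell below zero in 96% to 98% of runs. P1 and P97 had opposite signs in 40% to 52%, which would read as a change in spread.

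**Would ordinary pointwise 95% bands be enough?** Not across 33 correlated points. Under no change, the joint large-sample normal distribution of the quantiles (covariance of quantiles p ≤ q proportional to p(1−q) / (φ(z_p)φ(z_q)); 200 000 draws) gives at least one point outside its pointwise band in about 43% of countries. For the quantile shift minus the median shift, the figure is about 54%.

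**The case against.** The strongest reply is that these sentences only explain the axes. A point below zero does show a lower observed quantile in the later cohort, and the plan nowhere says that each point will be counted or reported as a population change. A reader might infer that noise is bound to be reported; the documents do not support that, because the authors may read the plots with caution. But the QQ sentence speaks of what segments of the population underwent, and nothing in the plan requires caution. The reply softens the point without removing it.

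A reader might also infer that research question 3 rests mainly on the plots. It does not: the plan names graphical and statistical approaches together and assigns multilevel models of the 5th and 95th percentiles to that question. It also asks about patterns, so one stray point in one country would not answer it.

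Finally, any single error rate depends on the chosen n, SD, shift and quantile. P1 is the noisiest of the 33 points, and pooling survey waves may make some cells large. That stands, and only a range is defensible. Small cells are still plausible at the edges of the age window. A 2005 survey of women aged 25 to 49 reaches 1980-89 births only at about age 25 (2005 − 25 = 1980), and a 2008 survey reaches 1950-59 births only at about age 49 (2008 − 49 = 1959).

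**Conclusion.** The point holds in a limited form. As written, the plan reads an observed quantile difference as a gain or loss without regard to its error, and it has no other test of a given quantile in a given country. The noise is two to three times the median's at the outermost plotted quantiles.

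Under the stated assumptions, a false loss at P1 ranges from 37% (500 women per cohort, true gain 0.5 cm) to 2% (5000 women, 1 cm), and at P5 from 28% to about 0%. Clustering would normally raise these figures. With cohorts well above 5000, few signs would be wrong; larger true shifts help too, though in small cohorts even a 1 cm gain leaves an appreciable error at P1.

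It would go too far to say that every plotted point becomes a gain or a loss. With heights recorded to 1 mm some differences are exactly zero: in the simulation with no change, P1 was off zero in 95% to 99.5% of runs. The plan should be changed on this point, but its answer to research question 3 does not stand or fall with it.

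**What to change.** 1. Add simultaneous 95% bands across the 33 quantiles to both plots. Obtain them from a bootstrap that resamples primary sampling units within strata and uses survey-weighted quantiles, for example taking the critical value from the bootstrap distribution of the maximum standardised deviation.
2. Reword the two reading rules. A point off the line shows the observed difference only. A gain or loss at a quantile is claimed only where the simultaneous band excludes zero.
3. Claim a disproportionate gain or loss only where the simultaneous band for the quantile shift minus the median shift excludes zero.

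No new data collection is needed, but the cost is more than rewording. The bootstrap needs programming, with unit, stratum and weight variables for each wave and a stated way of combining weights across pooled waves. The plots will be busier, and fewer tail changes will be claimable in small country-cohort cells. For scale, even the pointwise 95% half-width at P1 runs from ±2.78 cm (n = 500) to ±0.88 cm (n = 5000) with SD 6 cm and no design effect, and from ±4.58 cm to ±1.45 cm with SD 7 cm and a design effect of 2. Simultaneous bands are wider.

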**Statistical Analyses**

Using data from all countries and cohorts, multilevel regression models will constructed to examine the association between 1) mean height and SD of height (research question 2) and 2) median height and the 5^th^ and 95^th^ percentiles of height (research question 3)

Multilevel regression will be used to account for the nested structure of the data, as the outcome measures of interest (SD, 5^th^ percentile or 95^th^ percentile) is nested within cohort *i* at level 1 which is nested in country *j* at level 2.

The general statistical model at level 1 for standard deviation of height will be specified as:

$$\boldsymbol{Y}_{\boldsymbol{ij}}\boldsymbol{=}\boldsymbol{B}_{\boldsymbol{0}\boldsymbol{j}}\boldsymbol{+}\boldsymbol{B}_{\boldsymbol{1}}\boldsymbol{heigh}\boldsymbol{t}_{\boldsymbol{ij}}\boldsymbol{+}\boldsymbol{e}_{\boldsymbol{ij}}$$

where *y*_ij_ is the standard deviation (SD) of height in cohort *i* in country *j*, β_0j_ is the overall SD of height in each country, β_1_ is the slope of the relationship between mean height and SD of height, *height*_ij_ is the mean height in cohort *i* in country *j,* and e_ij_ is the residual for each cohort within countries.

The model at level 2 is represented as:

$$\boldsymbol{B}_{\boldsymbol{oj}}\boldsymbol{=}\boldsymbol{B}_{\boldsymbol{0}}\boldsymbol{+}\boldsymbol{u}_{\boldsymbol{0}\boldsymbol{j}}$$

where β_0_ is the grand mean SD of height across all countries and *u*_0j_ is the residual of the mean SD of height for country *j* from the overall of SD of height. Both models can be combined to obtain:

$$\boldsymbol{Y}_{\boldsymbol{ij}}\boldsymbol{=}\boldsymbol{B}_{\boldsymbol{0}}\boldsymbol{+}\boldsymbol{B}_{\boldsymbol{1}}\boldsymbol{heigh}\boldsymbol{t}_{\boldsymbol{ij}}\boldsymbol{+(}\boldsymbol{u}_{\boldsymbol{0}\boldsymbol{j}}\boldsymbol{+}\boldsymbol{e}_{\boldsymbol{ij}}\boldsymbol{)}$$

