**Outcome and Exposure**

Attained height (measured in centimeters) will be specified as a continuous variable, and is considered to be accurate to 1 millimeter (Macro International Inc. 2008). The standard deviation (SD) and the 5^th^ and 95^th^ percentiles will also be used as outcomes in statistical modeling because they provide information on how the distribution of height changes between and within countries over time.

The primary exposure of interest was considered to be cohort. To compare women over time, women will be divided into birth cohorts ranging from 1950-59, 1960-69, 1970-79, and 1980-89 within each country.

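### The percentile-on-median models for research question 3 have no reference slope; equal gains everywhere give a slope of 1, so finding an association cannot show which parts of the distribution moved most

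*SAP*

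**What the plan says.** The third aim, stated at the end of the Background, is to "determine whether patterns exist with regard to which parts of the height distribution experience the greatest height gains or losses across birth cohorts". That compares movement in one part of the distribution with movement in another.

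Under Statistical Analyses, "multilevel regression models will constructed to examine the association between" two sets of quantities. The second set, for this aim, is "median height and the 5^th^ and 95^th^ percentiles of height (research question 3"). The percentiles are listed as outcomes beside the SD: "the outcome measures of interest (SD, 5^th^ percentile or 95^th^ percentile) is nested within cohort".

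Only one equation follows, introduced by "The general statistical model at level 1 for standard deviation of height will be specified as", and only one slope is explained: "β_1_ is the slope of the relationship between mean height and SD of height". The percentile models have no equation, no reference value for the slope and no statement of how a given slope would be read.

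The SAP also plans QQ plots and mean-difference plots by country (Graphical Analyses), comparing the earliest and latest cohorts. No test or interval is attached to either.

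**The concern.** For the SD model, a slope of 0 is the natural benchmark: spread does not change as the mean changes. An analyst who carries the same template over to the percentile models will look for a slope that differs from 0. That benchmark is uninformative there. The 5th percentile, median and 95th percentile come from the same distribution and move together whenever the distribution moves.

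The idea that motivates the study in the Background is that dispersion stays roughly constant while the average moves. Under exactly that idea the percentile slopes are 1, so the scenario of equal gains everywhere gives a very strong association. One of the three aims could then be reported as answered by a result that would have appeared whatever the tails did.

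**Working it through.** The SAP gives no sample size, significance level or reference slope, so there is no planned figure to reproduce. Below, P5, P50 and P95 are the 5th, 50th and 95th percentiles.

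**1. Pure shift (no assumed inputs).** If only location changes, P5 = P50 − a and P95 = P50 + b with a and b constant. Both slopes on P50 are exactly 1.

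**2. Change in spread (normality assumed).** Let the SD change by g cm per cm of mean height. Then slope(P5) = 1 − 1.645g and slope(P95) = 1 + 1.645g.
- g = 0.05: 0.918 and 1.082.
- g = 0.1: 0.836 and 1.164.
- A zero slope for P5 needs g = 1/1.645 = 0.608; for P95 it needs g = −0.608.

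**3. Simulation of the SAP's random-intercept model.** Assumptions, none from the SAP: normal heights, SD 6 cm, between-country SD of means 2.5 cm, two-sided 5% Wald tests and 300 replicates per row. Four cohorts were taken in every country, the maximum that the SAP's cohort definition allows. The other inputs are in the table.

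| Countries / women per cell | g | Within-country SD of mean (cm) | Between-country SD of the spread (cm) | Mean slope P5 / P95 | Slope 0 rejected (both) | Slope 1 rejected P5 / P95 |
|---|---|---|---|---|---|---|
| 50 / 1000 | 0 | 0.7 | 0 | 0.994 / 0.993 | 100% | 7.3% / 8.7% |
| 50 / 1000 | 0 | 0.7 | 0.2 | 0.987 / 0.987 | 100% | 8.7% / 12.3% |
| 50 / 1000 | 0 | 0.3 | 0.2 | 0.985 / 0.983 | 100% | 10.7% / 11.7% |
| 50 / 1000 | 0 | 1.2 | 0.2 | 0.992 / 0.989 | 100% | 8.7% / 12.7% |
| 20 / 500 | 0 | 0.7 | 0.2 | 0.976 / 0.982 | 100% | 9.3% / 6.0% |
| 50 / 1000 | 0.05 | 0.7 | 0.2 | 0.906 / 1.068 | 100% | 100% / 88.7% |
| 50 / 1000 | 0.1 | 0.7 | 0.2 | 0.825 / 1.147 | 100% | 100% / 100% |
| 50 / 1000 | −0.1 | 0.7 | 0.2 | 1.151 / 0.824 | 100% | 100% / 100% |
| 20 / 500 | 0.1 | 0.7 | 0.2 | 0.821 / 1.139 | 100% | 100% / 91.0% |

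The slope-0 column never changes, so it carries no information about the tails. The slope-1 column separates the rows with g = 0 from the rest.

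**4. Why the slopes sit slightly below 1 when g = 0.** The regressor is an estimated median. For a normal sample, Var(P50) = 0.25σ²/(nφ(0)²) and Cov(P5, P50) = 0.05 × 0.5σ²/(nφ(1.645)φ(0)), with φ(0) = 0.3989 and φ(1.645) = 0.1031. Assume σ = 6.5 cm, n = 1000 and a within-country SD of the true median of 0.7 cm (variance 0.49).
- Var(P50) = 0.25 × 42.25/(1000 × 0.3989²) = 0.0664.
- Cov(P5, P50) = 0.025 × 42.25/(1000 × 0.1031 × 0.3989) = 0.0257.
- Purely within-country slope: (0.49 + 0.0257)/(0.49 + 0.0664) = 0.927.
- The same if the two errors were independent: 0.49/0.5564 = 0.881.
- With n = 300: (0.49 + 0.0856)/(0.49 + 0.2212) = 0.809, against 0.49/0.7112 = 0.689.
- Adding between-country variance 2.5² = 6.25, with no country differences in spread: (6.74 + 0.0257)/(6.74 + 0.0664) = 0.994.

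Noise in the median lowers the slope. The positive covariance with the tail percentile partly offsets this. The random-intercept model is affected little because it also uses the large differences between countries.

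**The case against.** The strongest reply is that the SAP plans no test of slope 0. It speaks of examining an association, names no null hypothesis or significance level for these models, and words the aim as a search for patterns. A reader might infer a plan to test against 0 and declare significance in every scenario; the text does not support that. Nor is a positive slope a strict algebraic necessity, as step 2 shows. The planned estimate is also usable, because a slope with its interval can be compared with 1. All of this stands. The defect is a missing reference value; the model itself is not invalid.

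The plots are a second reply. The mean-difference plot shows the change at each quantile by country, so tail and centre can be compared by eye. This helps only in part. The plot is read against zero, which shows gain or loss and not whether a tail outpaced the centre, and nothing measures its uncertainty. The QQ text also places a distribution that has only shifted on the line of equality, whereas a pure shift gives a line parallel to it.

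Three further inferences are tempting but not supported:
- That sampling error shared by tail and median causes the attenuation. Step 4 shows the sharing raises the slope.
- That slopes near 0.8 to 0.9 should be expected under a pure shift. Those belong to a purely within-country estimator, which the SAP does not specify.
- That cohort is absent from the models. The SAP states that "The primary exposure of interest was considered to be cohort", and cohort does index the level-1 units; it is not a predictor.

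**Conclusion.** The point holds as an omission with consequences. The percentile models for research question 3 have no reference slope, and the one benchmark the SAP's wording suggests, that of the SD model, does not carry over. That a pure shift gives slope 1 needs no assumptions. The near-certainty of an association rests on normality (0.608 cm of SD per cm of mean to remove it) and on the simulations, where slope 0 was rejected in 100% of replicates in all nine scenarios.

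Comparison with 1 is informative but slightly biased. With no change in spread, the mean slopes were 0.976 to 0.994 and slope 1 was rejected in 6% to 13% of replicates instead of 5%. With 300 replicates, the Monte Carlo standard error is √(0.06 × 0.94/300) = 1.4 to √(0.127 × 0.873/300) = 1.9 percentage points. These sizes depend on assumed numbers of countries, cell sizes and variances; the bias grows with smaller cells or a purely within-country slope. The SAP should be amended before analysis, since one of its three aims depends on how these slopes are read.

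**What to change.** 1. Write out the P5 and P95 models with the cohort median as predictor. State the reference value B1 = 1, report the estimate with a confidence interval, and say how to read each tail. For P5, B1 below 1 means the lower tail changes less than the median; for P95, B1 above 1 means the upper tail changes more. Each is a spreading of that half of the distribution as the median rises. Equivalently, model (P50 − P5) and (P95 − P50) on P50 with null 0. The second form is easier to read but carries the same small bias.

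2. Because of that bias, also report for each country (change in P5 − change in P50) and (change in P95 − change in P50) between cohorts, with null 0. Obtain confidence intervals from a bootstrap that respects strata and primary sampling units, and pool across countries. These contrasts have no error-prone regressor, and they address change across cohorts directly.

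The cost is a few lines of SAP text and a bootstrap on the same survey data. Results will look less emphatic than a very strong association with the median would.

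### Regressing the 5th and 95th percentiles on the median of the same cell biases both slopes below 1 under an equal shift: slightly in the planned pooled model, more in a within-country slope

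*SAP*

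**What the plan says.** Under Statistical Analyses, the models for the third aim relate "median height and the 5^th^ and 95^th^ percentiles of height (research question 3". The Analysis section describes a single summary database that "includes summary percentile values and 33-quantile values for the height distribution in each country for each birth cohort", so predictor and outcomes are computed from the same women.

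Only one model is written out: "The general statistical model at level 1 for standard deviation of height will be specified as". It has a random intercept for country and one common slope. Its predictor "is the mean height in cohort" *i* of country *j*, so the second aim already uses the cell mean. The percentile models have no equation of their own. No term allows for sampling error in the predictor, and no reference value for the slope is given.

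The third aim is to "determine whether patterns exist with regard to which parts of the height distribution experience the greatest height gains or losses across birth cohorts". The cohort definition allows up to four cells per country: "women will be divided into birth cohorts ranging from 1950-59, 1960-69, 1970-79, and 1980-89 within each country".

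**The concern.** A sample median is an estimate with error. When it serves as a predictor, error that the outcome does not share pulls the slope down. If every part of the height distribution moves by the same number of centimetres, the true slope of either percentile on the median is 1. The fitted slopes will nevertheless sit below 1 in both tails. Read against 1, that says both tails lag the middle when nothing of the kind has happened. The error is systematic, so adding countries does not average it away. It is largest when true differences between cells are small relative to the sampling error of the median, as with modest cohort changes inside one country.

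**Working it through.** The SAP states no cell size, variance or expected slope, so it has no figure to reproduce.

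**Inputs.** From the SAP: predictor, outcomes, random-intercept structure, up to four cohorts per country. Assumed: within-cell SD 6 cm, between-country SD of means 2.5 cm, within-country cohort SD 0.5 cm, *n* = 1000 to 3000 women per cell, normal heights and an equal shift. The survey sizes under Data Sources count households and do not fix *n*.

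**Step 1: shared error.** For sample quantiles at p ≤ r, the covariance is p(1−r)/(n·f_p·f_r), with f the density at the quantile. In units of SD²/n:
- Variance of the median: 0.25/0.3989² = 1.571.
- Covariance of the 5th percentile with the median: 0.05 × 0.5/(0.1031 × 0.3989) = 0.608. By symmetry the 95th gives the same.
- Shared fraction: 0.608/1.571 = 0.387, about 39%.

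**Step 2: slope on the median.** With τ² the true variance of the cell medians and v = 1.571·SD²/n, the slope is (τ² + 0.387v)/(τ² + v).

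Within country, τ² = 0.5² = 0.25:
- n = 1000: v = 1.571 × 36/1000 = 0.0566; slope (0.25 + 0.0219)/(0.25 + 0.0566) = 0.887.
- n = 3000: v = 0.0189; slope (0.25 + 0.0073)/(0.25 + 0.0189) = 0.957.

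All cells together, τ² = 6.25 + 0.25 = 6.50:
- n = 1000: (6.50 + 0.0219)/(6.50 + 0.0566) = 0.995.
- n = 3000: (6.50 + 0.0073)/(6.50 + 0.0189) = 0.998.

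**Step 3: slope on the mean.** For normal data the gap between a sample quantile and the sample mean is independent of the mean. Their covariance therefore equals the variance of the mean, SD²/n, and the slope is (τ² + SD²/n)/(τ² + SD²/n) = 1.

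**Step 4: the planned model.** The random-intercept slope mixes within- and between-country information. The more the country SDs differ, the larger the intercept variance of the percentiles and the more weight falls on within-country contrasts. Simulated equal shifts with normal heights gave:

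| Setting | Slope on median | Slope on mean |
|---|---|---|
| Equal country SDs | 0.995-0.998 | about 1.00 |
| Country SDs differ by 0.3 cm | 0.975-0.988; slope 1 rejected in 7-20% of datasets | about 1.00; rejected in 5-7% |
| Country SDs differ by 0.6 cm (SD 6.5 cm, between-country SD 3 cm, n = 500-1000) | 0.93-0.95 | 0.99-1.01 |

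**Step 5: non-normal heights.** Simulated with SD 6.5 cm, n = 500 and cohort SD 0.5 cm (5th / 95th percentile slopes):

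| Shape | Planned, median | Planned, mean | Within-country, median | Within-country, mean |
|---|---|---|---|---|
| Skew 0.2 | 0.973 / 0.982 | 0.994 / 1.007 | 0.778 / 0.811 | 0.971 / 1.049 |
| Skew 0.5 | 0.974 / 0.980 | 0.990 / 1.009 | 0.773 / 0.810 | 0.927 / 1.095 |
| t, 6 d.f. | 0.992 / 0.996 | 1.008 / 1.013 | 0.898 / 0.887 | 1.097 / 1.085 |

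Under skew the mean brings each slope nearer 1 but puts the tails on opposite sides of it. Under heavy tails it leaves both slopes about as far above 1 as the median leaves them below.

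**The case against.** Several points on the other side stand.

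- **Size.** A reader might infer that the reported slopes will be 10% or more too low. The documents do not support that. Such figures belong to a purely within-country slope, whereas the SAP fits one pooled slope that also draws on differences between countries. With equal country SDs that slope is hardly distinguishable from 1.
- **Reference value.** A reader might infer that the SAP tests against 1. It names no reference slope. The value follows only from the aim, because an equal shift gives 1.
- **The remedy.** A reader might infer that the mean removes the bias outright. It does so only for normal heights, which the SAP does not claim. With skew 0.5 the false gap between the two tails in the within-country slope grows from 0.810 − 0.773 = 0.037 on the median to 1.095 − 0.927 = 0.168 on the mean. In the planned model it grows from 0.006 to 0.019.
- **Choice of predictor.** A median predictor for percentile outcomes is coherent, and it is robust to recording errors inside the 100-200 cm limits. Use of the mean for the second aim creates no obligation for the third.
- **Other evidence.** The third aim is also addressed by QQ and mean-difference plots, which compare quantile shifts without regressing on an estimated median.

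These points limit the size of the concern and qualify the remedy. They do not change the mechanism or the direction for normal or mildly skewed heights.

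**Conclusion.** The concern holds in a limited form. As planned, sampling error in the median pulls both percentile slopes below 1 under an equal shift. With 1000 to 3000 women per cell, SD about 6 cm and cohort SD 0.5 cm, the bias is about 0-3% in the pooled random-intercept model and about 4-12% in a within-country slope. It reaches about 5-7% in the pooled model if country SDs differ by 0.6 cm, in runs with 500 to 1000 women per cell.

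All sizes rest on assumed inputs. Larger cells or larger cohort changes shrink the bias; the clustering described under Data Sources would tend to enlarge it by raising the error of the median. The consequence is confined to reading the slopes against 1. It does not invalidate the third aim, but the correction is cheap and the bias has a known direction.

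**What to change.** - In Statistical Analyses, make mean height of the cell the predictor in the 5th and 95th percentile models, as in the SD model, and report the median-based slopes alongside.
- State that an equal shift corresponds to a slope of 1, so that the reader knows what the slopes are compared with.
- Report skewness and tail weight within cells. If heights depart clearly from normal, say that a small gap between the two slopes (skew) or slopes slightly above 1 in both tails (heavy tails) may be an artefact.

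The cost is one change of predictor in the text and code, a second set of slopes, and a simple distributional check. The drawback is that the mean is slightly more sensitive than the median to gross recording errors that survive the 100-200 cm limits. The median-based results reported alongside help to show whether this matters.
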